### Primary analysis

The effect of condition (MBCT + TAU vs. TAU) on the primary outcome measure (depressive symptoms) will be examined using general linear models. Condition and baseline score of depressive symptoms will be included as independent variables, depressive symptoms at FU1 as the dependent variable. Because MBCT is delivered in mixed groups consisting of regular patients and a few study participants and previous studies did not yield an effect of therapy group [20], we will not incorporate a random group effect.

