### Procedure

**Assessment of eligibility, baseline measures and randomization**

All patients who indicated their interest in the study are invited for a research interview. Written informed consent is obtained during this first appointment. To assess eligibility and to classify comorbid psychiatric disorders, participants are interviewed by a research psychologist or psychiatrists in training with the depression, anxiety, psychosis and addiction modules of the Mini International Neuropsychiatric Interview (MINI; [25]). In addition, the following disorder-related characteristics are assessed: duration of current major depressive episode, number of psychological treatment sessions (i.e. CBT and/or IPT) during current major depressive episode, duration and doses of pharmacological treatments during the current depressive episode, number of depressive episodes during lifetime and age of onset. On the base of these details the research assistant fills out the Dutch Measure for quantification of Treatment Resistant Depression (DM-TRD, [26] [27]). After completion of the baseline questionnaires, a computer program is used to randomly allocate patients to either MBCT + TAU or TAU. A minimization strategy is used for severity of symptoms (IDS-SR ≥21 and ≤31 vs. > 31 and ≤ 39 vs. > 39) and duration of major depressive episode (1–2 years vs. > 2 years). If the period between randomization and start of the MBCT training exceeds four weeks in the MBCT + TAU condition, a repeated baseline assessment takes place.

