### Statistical analyses

**Power analysis and sample size**

A power analysis was executed based on the findings of van Aalderen et al. [20]. Van Aalderen and colleagues [20] reported an effect size of 0.53 (Cohen’s *d*) in a sample of 69 currently depressed patients. Based on an alpha of 0.05 and power of 80 %, estimating the correlation between baseline and first follow-up measurements to be 0.5 and intending to use an ANCOVA controlling for baseline levels of depression, a needed sample size of 43 per condition was calculated. Expecting a drop-out of 8 patients, a total of 94 participants will be recruited.

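### Episode duration is a minimisation factor but is absent from the primary model; if it is prognostic, the standard error is slightly too large and a little power is left unused

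*Protocol article*

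**What the plan says.** The subsection of the protocol article on eligibility, baseline measures and randomization names two allocation factors. "A minimization strategy is used for severity of symptoms", in three IDS-SR bands, is the first; the second is "duration of major depressive episode (1–2 years vs. > 2 years".

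The Primary analysis section fixes the terms of the general linear model: "Condition and baseline score of depressive symptoms will be included as independent variables, depressive symptoms at FU1 as the dependent variable". The Secondary analyses section carries the same specification over to quality of life, rumination, mindfulness skills and self-compassion, and assigns a χ² test to remission.

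The sample size rests on the same baseline-only model, "intending to use an ANCOVA controlling for baseline levels of depression". Elsewhere in the analysis, duration serves only to define subgroups in which the primary and secondary analyses are repeated (Analyses plan).

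**The concern.** Minimisation removes most of the chance imbalance in duration between the arms. A model without duration still counts the variation that duration explains as residual noise, although that variation now contributes little to the difference between arms. If duration predicts the outcome once baseline IDS-SR is in the model, the reported standard error exceeds the true sampling error of the estimate. The confidence interval is then too wide and the test rejects less often than 5% under the null.

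The article names the covariates explicitly, so this concerns a stated choice and not a detail left to an analysis plan. At stake is some precision that the allocation has already secured and that the stated model does not use.

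**Working it through.** **Inputs from the article (Power analysis and sample size).** "Based on an alpha of 0.05 and power of 80" per cent; "reported an effect size of 0.53" (Cohen's d); "estimating the correlation between baseline and first follow-up measurements to be 0.5"; "a needed sample size of 43 per condition was calculated". The article does not say whether the test is two-sided; a two-sided test reproduces its figure.

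**Input assumed.** r is the share of the residual variance, after baseline IDS-SR, that duration explains (partial R²). The article gives no value. The range shown is 0 to 0.10.

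**1. Reproduce the planned sample size.** Adjusting for baseline leaves a residual variance of 1 − 0.5² = 0.75.
- Normal approximation: n = 2 × (1.96 + 0.8416)² × 0.75 / 0.53² = 41.9, so 42 per arm.
- Noncentral t with one covariate: 43 per arm, power 80.1%.
- One-sided testing would give 34 and an unadjusted comparison 56 (normal approximation). Neither matches.

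The stated 43 is therefore right for the stated model.

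**2. Excess in the standard error when duration is omitted.** Under good balance the ratio is 1/√(1 − r).

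**3. Power with duration added.** Noncentral t, two covariates, residual variance 0.75 × (1 − r), 43 per arm.

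**4. Power with duration omitted.** Balance also reduces the true variance of the estimate in the omitting model, and this has to be counted. The model-based standard error is √(0.75 × 2/43) = 0.187, the noncentrality is 0.53/0.187 = 2.84 and the critical value is 1.99 (83 df). Power is then about Φ((2.84 − 1.99)/√(1 − r)). At r = 0.10 this is Φ(0.85/0.949) = Φ(0.896) = 81.5%. At r = 0 the table shows the noncentral t value from step 1.

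**5. Size of the omitting test under good balance.** 2 × (1 − Φ(1.96/√(1 − r))).

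| Assumed r | SE excess | Power, omitted | Power, added | Gain (points) | Size, omitted |
|---|---|---|---|---|---|
| 0 | 0% | 80.1% | 80.1% | 0 | 5.0% |
| 0.02 | 1.0% | 80.5% | 80.9% | 0.4 | 4.8% |
| 0.05 | 2.6% | 80.8% | 82.0% | 1.2 | 4.4% |
| 0.10 | 5.4% | 81.5% | 84.0% | 2.5 | 3.9% |

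**6. Check by simulation.** Minimisation was simulated with 86 patients and 4,000 runs per setting, assuming a 50:50 split on duration and a biased coin of 0.8.
- r = 0: mean standard error 0.186 with and without duration; power 80.5% in both models.
- r = 0.05: power 80.9% omitted, 82.3% added.
- r = 0.10: standard error 0.187 against 0.177; power 81.5% against 84.0%; null rejection with duration omitted 4.5%.

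The Monte Carlo standard error of a null rejection rate is √(0.05 × 0.95/4000) = 0.3 points. The 4.5% is closer to nominal than the formula's 3.9%, partly because simulated balance is imperfect and partly through simulation error. The direction is the same.

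**The case against.** The strongest reply is that nothing is lost against the plan. The trial was sized for a baseline-only ANCOVA, the primary model is that ANCOVA, and 43 per condition delivers the declared power. That stands: a reader might infer that the trial falls short of 80%, but the sample size never relied on duration.

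The second reply is that duration may not be prognostic here. This also stands. A reader might take the Background as evidence that it is, because it reports that recovery all but stops after one year. That statement, and the rationale for recruiting from 12 months, concern a threshold that every participant has already passed. They do not show that 1–2 years and more than 2 years differ in outcome. The planned subgroup repeats ask whether the treatment effect varies with duration, which is a different question from prognosis.

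A reader might also compare 80.1% with 84.0% at r = 0.10 and call the gain about 4 points. That credits balance in the size of the test but ignores it in the power of the omitting model. Counted in both, the gain is 2.5 points.

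Nor do the documents support a reading of bias or of excess false positives. The error runs in the conservative direction, and severity is already adjusted for on its continuous scale.

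What survives is that the trial balances on a factor that its analysis then leaves out, and that including it costs next to nothing.

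**Conclusion.** The point holds as a minor matter of efficiency and of consistency between allocation and analysis. Across an assumed partial R² of 0 to 0.10, the standard error of the stated model is 0% to 5.4% too large, and adding duration gains 0 to about 2.5 points of power. Up to 0.05 the figures are at most 2.6% and about 1.2 points. They rest on that assumed range, on good balance on duration, and on the article's own effect size and correlation. If duration carries no information beyond baseline IDS-SR, the two models perform alike. The planned power is met, the estimate is unbiased, and validity is not in question.

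**What to change.** State the primary model as: FU1 IDS-SR on condition, continuous baseline IDS-SR and episode duration (1–2 versus more than 2 years, coded as in the minimisation). Add the same duration term to the general linear models for quality of life, rumination, mindfulness skills and self-compassion. The χ² test for remission takes no covariate; adjusting that outcome as well would need a logistic model. In the repeats within duration subgroups the term drops out.

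The cost is a few words and one degree of freedom per model. Duration is recorded before randomisation, so no new data are needed. If duration proves uninformative, power at 43 per condition stays at 80.1%. Naming the term in advance also removes any later choice of covariates.

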#### Possibly moderating variables

### Treatment-resistance

The Dutch Measure for quantification of Treatment Resistant Depression (DM-TRD; [26, 27]) is used to investigate treatment-resistance of the current depressive episode. With the DM-TRD several dimensions of treatment-resistance are scored by the clinician (duration, symptom severity, functional impairment, comorbid anxiety symptoms, prosocial stressors, treatment failures of pharmacological and psychological treatment) which leads to a total score ranging from 2–26.

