### Childhood trauma

To assess the experience of traumatic childhood events, participants fill out the Childhood Trauma Questionnaire (CTQ-SF; [40]). This 28-item questionnaire measures traumatic experiences and maltreatment during childhood. The CTQ-SF has previous been validated in a Dutch clinical sample [41].

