### Secondary analyses

Effects on quality of life, rumination, mindfulness skills, and self-compassion will also be investigated using general linear models with the same independent variable as in the primary analysis. To investigate effects on remission rates a χ^2^ test will be performed. Moderating effects of level of treatment-resistance and childhood trauma will be investigated by including an interaction effect (condition*moderator) in the models. Furthermore, exploratory analyses on rumination, mindfulness skills and self-compassion as possible underlying mechanisms of change will be conducted. Consolidation and moderation of treatment effect will be investigated in the whole sample of MBCT completers (MBCT + TAU and TAU) using end-of-treatment assessments and follow-up assessments at three and six months after end of treatment.

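### An inexpensive gain in precision is left unused: the primary model adjusts only for baseline IDS-SR, although DM-TRD and CTQ are also measured before randomisation

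*Protocol article*

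**What the plan says.** The Primary analysis section of the protocol article names the model for IDS-SR at the first follow-up: "Condition and baseline score of depressive symptoms will be included as independent variables". No other covariate is listed. This matches the Power analysis and sample size section, where the authors are "intending to use an ANCOVA controlling for baseline levels of depression".

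DM-TRD and CTQ appear under Possibly moderating variables. The first "is used to investigate treatment-resistance of the current depressive episode"; for the second, "participants fill out the Childhood Trauma Questionnaire". Table 1 marks both at baseline only, and the Procedure section places allocation after the baseline questionnaires. Their one stated use in the analysis is in Secondary analyses, where moderation is examined "by including an interaction effect (condition*moderator) in the models".

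**The concern.** In a linear model, a covariate measured before randomisation and related to outcome reduces residual variance without changing what the treatment coefficient estimates. DM-TRD covers functional impairment, comorbid anxiety, stressors and previous treatment failures, and CTQ covers childhood maltreatment. Neither is simply another reading of baseline IDS-SR, so either could carry further prognostic information. The covariate list is stated in the article, so the choice has been made rather than left open.

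The stake is limited. The trial is sized with almost no margin above 80% power, and some precision may be available from data already being collected. The validity of the result is not at stake.

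**Working it through.** **Inputs from the Power analysis and sample size section**
- Significance level and power: "Based on an alpha of 0.05 and power of 80" per cent. Sidedness is not stated; two-sided is assumed because it reproduces the stated sample size.
- Effect: the source study "reported an effect size of 0.53 (Cohen’s *d*) in a sample of 69 currently depressed patients", so d = 0.53.
- Correlation: "estimating the correlation between baseline and first follow-up measurements to be 0.5", so r = 0.5.
- Stated result: 43 per condition, 86 in all; adding 8 for drop-out gives 94.

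**Input the article does not give**
- The share of first follow-up IDS-SR variance, left after baseline IDS-SR, that DM-TRD and CTQ jointly explain (partial R²). Assumed range: 0 to 0.10.

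**Step 1: reproduce the plan's figure**
- Residual variance factor: 1 − 0.5² = 0.75.
- Standard error in SD units at 43 per condition: √(0.75 × 2/43) = √0.03488 = 0.1868.
- Noncentrality: 0.53/0.1868 = 2.838.
- Degrees of freedom with one covariate: 86 − 2 − 1 = 83.
- Noncentral t power, two-sided 5%: 80.1% at 43 per condition and 79.1% at 42. The stated 43 is reproduced exactly.
- Alternatives do not fit. By normal approximation, a two-sided comparison without a covariate needs 56 per condition and a one-sided ANCOVA needs 34.

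**Step 2: add the two scores**
- Residual variance factor: 0.75 × (1 − R²).
- Standard error: 0.1868 × √(1 − R²).
- Degrees of freedom with three covariates: 86 − 2 − 3 = 81.
- Equivalent extra patients: 86/(1 − R²) − 86.

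| Assumed partial R² | Standard error (SD units) | Change in SE | Noncentrality | Power at 43 per condition | Equivalent extra patients |
|---|---|---|---|---|---|
| 0 | 0.1868 | none | 2.838 | 80.1% | 0 |
| 0.02 | 0.1849 | −1.0% | 2.867 | 80.9% | 1.8 |
| 0.05 | 0.1820 | −2.5% | 2.911 | 82.0% | 4.5 |
| 0.10 | 0.1772 | −5.1% | 2.991 | 84.0% | 9.6 |

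**Step 3: cost if the scores predict nothing**
- Power is 80.09% with 83 degrees of freedom and 80.06% with 81. The loss is 0.03 percentage points, which disappears on rounding.

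**The case against.** The strongest case against acting is that nothing here is wrong. ANCOVA on baseline IDS-SR is prespecified, valid and the same model as the one behind the sample size. A short covariate list is a legitimate choice when the prognostic value of other scales is unknown. DM-TRD includes symptom severity and episode duration: severity is already in the model through IDS-SR, and the minimisation uses both. Its added information may therefore be small. The Aims section asks whether the two measures alter the treatment effect; it does not say that they are expected to predict outcome. Nor is the adjustment quite free, because missing baseline scores need a rule. All of this stands. It makes the point an optional improvement with a modest and uncertain gain.

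Two stronger readings are tempting, and the document supports neither.

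- **Biased primary estimate.** A reader might infer that chance imbalance in DM-TRD or CTQ biases the primary result. Under randomisation, such imbalance is part of the sampling variation that the ANCOVA standard error already reflects. It is the same cost as the lost precision and must not be counted again.
- **False moderation.** A reader might infer that the moderator models omit the moderator's own main effect, so that a merely prognostic score would look like a moderator. Secondary analyses says only that moderation is examined "by including an interaction effect (condition*moderator) in the models". It does not exclude the main effect, and adding an interaction is ordinarily understood to keep both main effects. In simulation with 86 patients and no true interaction, omitting the main effect gives false-positive rates of about 30% at a standardised prognostic slope of 0.2 and 62% at 0.3. Those rates need both that unstated omission and 0/1 coding of condition. With the main effect included, or with ±0.5 coding, the rate is close to 5%.

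**Conclusion.** This is a low-cost improvement and not a defect. The planned primary estimate remains valid and has its stated power. Using DM-TRD and CTQ as covariates would lower the standard error by about 1% to 5% and bring power to between 80.9% and 84.0%, provided that they jointly explain 2% to 10% of the variance left after baseline IDS-SR. That range is an assumption; the article has no figure from which to derive it. Given the overlap of DM-TRD with severity and duration, the lower end is plausible, and a nil gain is possible. Even then power stays at 80.1%, so the adjustment has practically no downside. No claim of bias from imbalance or of false moderation findings is made.

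**What to change.** In Primary analysis, list four independent variables: condition, baseline IDS-SR, DM-TRD total and CTQ total. Both totals should be continuous and taken from the assessment before randomisation. The last point needs stating because the Procedure section allows a repeated baseline after randomisation in the MBCT arm only. Add that a missing DM-TRD or CTQ total is replaced by the mean over all randomised patients, computed without regard to arm, so that no patient is lost for want of a baseline score. Fix the change before any outcome data are compared by condition.

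Secondary analyses refers back to the primary model's independent variables, so the text should also say whether the extra covariates carry over to the other continuous outcomes.

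The cost is two degrees of freedom, about two sentences of text and no additional data collection. The sample size need not change.

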### Secondary analyses

Effects on quality of life, rumination, mindfulness skills, and self-compassion will also be investigated using general linear models with the same independent variable as in the primary analysis. To investigate effects on remission rates a χ^2^ test will be performed. Moderating effects of level of treatment-resistance and childhood trauma will be investigated by including an interaction effect (condition*moderator) in the models. Furthermore, exploratory analyses on rumination, mindfulness skills and self-compassion as possible underlying mechanisms of change will be conducted. Consolidation and moderation of treatment effect will be investigated in the whole sample of MBCT completers (MBCT + TAU and TAU) using end-of-treatment assessments and follow-up assessments at three and six months after end of treatment.

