## Methods/Design

### Design

This study is a multi-center open-labeled randomized controlled trial with two groups: MBCT+ TAU vs. TAU. The study has been approved by the Medical Ethics Committee Arnhem-Nijmegen (nr. 2012/339) for all participating sites. Before randomization, written informed consent is obtained from all participants. Primary and secondary outcome measures are assessed at baseline and after MBCT + TAU (8–12 weeks) or after a TAU-period (8–12 weeks). Participants allocated to the TAU condition are offered participation in the MBCT after completion of the TAU-period and first follow-up assessment. Of all participants who completed the MBCT, follow-up measures take place at three and six months after the end of treatment. For an overview of the recruitment and measurement points see Fig. 1.

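### The covariate rule for the four continuous secondary outcomes, as written, leaves out each outcome's own baseline score

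*Protocol article*

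**What the plan says.** The Primary analysis section of the protocol article sets out a general linear model for IDS-SR at the first follow-up (FU1): "Condition and baseline score of depressive symptoms will be included as independent variables".

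The Secondary analyses section then turns to the other continuous outcomes. "Effects on quality of life, rumination, mindfulness skills, and self-compassion will also be investigated", and the method is "general linear models with the same independent variable as in the primary analysis". Variable is in the singular here, while the primary model has two. No model in the article names the baseline score of a secondary outcome.

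Those scores are collected. Under Design, "Primary and secondary outcome measures are assessed at baseline", and Table 1 marks WHOQOL-BREF, RRS-EXT, FFMQ and SCS at baseline as well as at FU1.

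On allocation, "A minimization strategy is used for severity of symptoms", together with duration of the episode. None of the four secondary scales is a minimization factor.

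**The concern.** For a continuous outcome measured before and after treatment, the usual adjustment is for the baseline of that same outcome, because it is normally the best single predictor available. The primary model does this. The secondary rule carries over the primary model's variables, and the only baseline among them is depressive symptoms.

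The sentence can be read in three ways:

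- (a) condition plus baseline IDS-SR, which is the literal reading if both variables carry over;
- (b) condition only, if the singular is taken at face value;
- (c) the same structure, with each outcome's own baseline in place of baseline IDS-SR.

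Under (a) and (b) a covariate already in hand goes unused in four comparisons. Three of these outcomes (rumination, mindfulness skills, self-compassion) are also the candidate mechanisms of change. Under (c) the model is sound, but the words do not state it. An open choice among the three also allows the covariate to be settled after the data have been seen.

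**Working it through.** **Inputs from the article** (Power analysis and sample size): effect size 0.53, alpha 0.05, power 80%, 43 per condition, drop-out of 8, total 94, and "estimating the correlation between baseline and first follow-up measurements to be 0.5". That correlation is stated for depression.

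**Assumptions made here.** The article gives no effect size or correlation for a secondary outcome. For illustration, d = 0.53 and an own-baseline correlation r = 0.5 are borrowed from the primary outcome. The correlation c between baseline IDS-SR and a secondary outcome at FU1 is varied from 0.1 to 0.5.

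**Step 1: reproduce the plan's sample size.** ANCOVA leaves a residual variance factor of 1 − r² = 1 − 0.25 = 0.75.

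- Normal approximation: n per arm = 2 × 0.75 × (1.960 + 0.842)² / 0.53² = 41.9, so 42.
- Noncentral t with 2n − 3 degrees of freedom, two-sided 0.05: 42 per arm gives 79.1% and 43 per arm gives 80.1%.
- 2 × 43 + 8 = 94.

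Both stated figures reproduce.

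**Step 2: change the covariate.** With baseline IDS-SR as the only covariate the factor is 1 − c². The noncentrality is 0.53 / √(factor × 2/43). The share of the own-baseline gain that is lost is 1 − c²/0.25.

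| Model | Variance factor | Ratio to 0.75 | Gain lost | Power, 43 per arm |
|---|---|---|---|---|
| Own baseline, r = 0.5 | 0.75 | 1.00 | 0% | 80.1% |
| IDS-SR only, c = 0.5 | 0.75 | 1.00 | 0% | 80.1% |
| IDS-SR only, c = 0.4 | 0.84 | 1.12 | 36% | 75.5% |
| IDS-SR only, c = 0.3 | 0.91 | 1.21 | 64% | 72.1% |
| IDS-SR only, c = 0.2 | 0.96 | 1.28 | 84% | 69.8% |
| IDS-SR only, c = 0.1 | 0.99 | 1.32 | 96% | 68.5% |
| Condition only | 1.00 | 1.33 | 100% | 68.1% |

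More than half the gain is lost only when c² < 0.125, that is, when c is below about 0.354.

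**Step 3: chance imbalance.** The standard error of a baseline difference at 43 per arm is √(2/43) = 0.22 SD, so an imbalance of 0.2 SD is ordinary. Let b be the baseline correlation between IDS-SR and the secondary scale. If IDS-SR is balanced, the part of the imbalance that passes into an IDS-SR-adjusted estimate has slope (r − bc)/(1 − b²):

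- b = 0.5, c = 0.1: (0.5 − 0.05)/0.75 = 0.60, and 0.60 × 0.2 = 0.12 SD;
- b = 0.5, c = 0.4: (0.5 − 0.20)/0.75 = 0.40, and 0.40 × 0.2 = 0.08 SD.

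Over b from 0.2 to 0.5 and c from 0.1 to 0.4 the shift lies between 0.08 and 0.12 SD. This is the same loss as in Step 2 seen in a single trial, and should not be added to it.

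**The case against.** The strongest objection is textual. The article nowhere says that baseline depression replaces the own baseline. The singular noun leaves reading (c) open, and measuring every scale at baseline fits that reading. A condensed article may also leave exact covariates to a fuller document. The first part stands: the omission is one reading, though the literal one. The second stands only in part. The article is not silent here. It gives a covariate rule, and followed as written that rule supplies either the wrong baseline or none.

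Three stronger conclusions that a reader might draw are not supported:

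- *That most of the ANCOVA gain is thrown away.* This needs a cross-correlation below about 0.35 when r = 0.5, and the documents give no such figure. At 0.4 the loss is 36%.
- *That baseline imbalance goes uncorrected, or that the results are biased.* Adjusting for IDS-SR removes the part of an imbalance that is shared with depression. Randomization keeps the estimate unbiased on average.
- *That the trial falls short of its promised power.* The 80% is stated for depressive symptoms. No power is claimed for any secondary outcome, so the percentages above show relative efficiency only.

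It would also go too far to require episode duration in these models. The primary model does not contain it, and nothing in this point argues for it.

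**Conclusion.** The point holds as a badly fixed covariate rule. On the literal reading, and on the condition-only reading, the four continuous secondary models omit a baseline score that the trial collects. Only the matching-baseline reading is sound, and the text does not state it.

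The cost is lower precision and incomplete correction of chance imbalance. Under the borrowed assumptions, residual variance would be 12% to 32% larger than with the own baseline for c from 0.4 to 0.1, and there would be no loss at c = 0.5. These sizes rest on d and r taken from the primary outcome and on an assumed range for c. The primary analysis and the sample size stand as they are.

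**What to change.** Replace the covariate clause in Secondary analyses with: *Each continuous secondary outcome at FU1 is regressed on condition and the baseline score of that same outcome.* Baseline IDS-SR may be kept as an additional covariate, since symptom severity is a minimization factor; if so, say so explicitly. The wording should be settled before outcome data by condition are examined.

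The cost is one sentence. No new data are needed, and neither the primary model nor the sample size changes.

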#### Secondary outcome measures

### Remission rates

Remission from depression according to DSM-IV criteria is assessed with the major depression module of the Mini International Neuropsychiatric Interview (MINI; [25]).

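### Remission is tested with an unadjusted chi-square test, which is valid but gives up a modest amount of power that adjustment for the minimisation factors would recover

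*Protocol article*

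**What the plan says.** All places are in the Protocol article.

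- **Outcome (Remission rates).** "Remission from depression according to DSM-IV criteria is assessed with the major depression module" of the MINI, so the outcome is binary and interview-based.
- **Test (Secondary analyses).** "To investigate effects on remission rates a χ^2^ test will be performed". No covariate is named.
- **Primary analysis.** A general linear model for IDS-SR at the first follow-up: "Condition and baseline score of depressive symptoms will be included as independent variables". Episode duration is not in this model.
- **Continuous secondary outcomes (Secondary analyses).** These are analysed "using general linear models with the same independent variable as in the primary analysis".
- **Allocation (Assessment of eligibility, baseline measures and randomization).** "A minimization strategy is used for severity of symptoms" in three IDS-SR bands, and for "duration of major depressive episode" in two categories.
- **Moderation (Secondary analyses).** Treatment resistance and childhood trauma "will be investigated by including an interaction effect (condition*moderator) in the models". The outcomes concerned are not listed.
- **Power analysis and sample size.** 43 per condition for the primary outcome, 94 in total. No power figure is given for remission.

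**The concern.** The chi-square test is a stated choice, so this is not detail left to a fuller plan. It makes remission the only efficacy outcome analysed without a covariate. Everyone has a current depressive episode at entry, so remission has no informative baseline value of its own. Baseline IDS-SR is the natural stand-in and is already collected.

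The trial also balances the arms on severity and duration and then leaves both out of this test. If these factors predict remission, the unadjusted test works with a standard error that is too large for the balanced design. It becomes somewhat conservative and loses power. Remission is easy for clinicians to read, and a trial of this size has limited power for it in any case. Power that can be recovered from data already in hand is therefore worth having.

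**Working it through.** **1. The plan's own sample size.** Inputs from Power analysis and sample size: d = 0.53, correlation 0.5, alpha 0.05 (taken as two-sided), power 80%.

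Normal approximation: n = 2 × (1.960 + 0.842)² × (1 − 0.5²) / 0.53² = 2 × 7.85 × 0.75 / 0.2809 ≈ 41.9, so 42 per arm. With the noncentral t distribution, power is 0.791 at 42 and 0.801 at 43, so 43 is right. Total: 2 × 43 + 8 = 94. Both figures reproduce, and nothing below changes them.

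**2. Power of the unadjusted comparison.** Remission rates are assumed. For 20% vs 40% with 43 per arm, the mean rate is 0.30.

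- Null standard error: √(2 × 0.30 × 0.70 / 43) = 0.0988
- Alternative standard error: √((0.20 × 0.80 + 0.40 × 0.60) / 43) = 0.0964
- Power: Φ((0.20 − 1.96 × 0.0988) / 0.0964) = Φ(0.065) ≈ 53%

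The same formula gives 64% for 10% vs 30% and 47% for 30% vs 50%.

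**3. Gain from adjustment, latent-threshold simulation.** There are 86 patients, minimised on severity and duration. Remission is a cut on a normal variable that has correlation ρ with baseline severity. Chi-square power is compared with that of adjusted logistic regression (2,500 runs per scenario):

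| Assumed remission, TAU vs MBCT + TAU | ρ = 0.3 | ρ = 0.5 |
|---|---|---|
| 20% vs 40% | 56% vs 59% | 54% vs 60% |
| 20% vs 45% | 72% vs 74% | 71% vs 79% |
| 30% vs 55% | 67% vs 69% | 67% vs 74% |

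The gains are 3, 2 and 2 points at ρ = 0.3, and 6, 8 and 7 points at ρ = 0.5. At ρ = 0.2 the gain is 1 to 2 points. The Monte Carlo standard error of one power figure is at most √(0.25 / 2500) = 1 point. Repeat runs gave 2 to 4 points at ρ = 0.3 and about 7 at ρ = 0.5.

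**4. False-positive rate and sensitivity, logistic simulation.** There are 86 patients, 80/20 biased-coin minimisation, 4,000 runs, and a conditional log odds ratio of 1.1 when there is an effect. Prognostic strength is set by log odds ratios per SD of severity and for longer duration:

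| Strength (severity, duration) | Type I error, chi-square vs adjusted | Power, chi-square vs adjusted |
|---|---|---|
| Weak (−0.5, −0.5) | 0.046 vs 0.050 | 0.65 vs 0.67 |
| Moderate (−1.0, −0.5) | 0.043 vs 0.053 | 0.53 vs 0.60 |
| Strong (−1.5, −1.0) | 0.028 vs 0.045 | 0.40 vs 0.54 |

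Compare within rows only. The marginal remission difference shrinks down the table: 0.523 − 0.280 = 0.243, then 0.520 − 0.306 = 0.214, then 0.517 − 0.333 = 0.184. The Monte Carlo standard error at 5% is √(0.05 × 0.95 / 4000) ≈ 0.003. The chi-square test is thus near nominal with weak predictors and clearly conservative with strong ones. The strong row (gain 0.537 − 0.402 ≈ 14 points) is an extreme in which both factors predict remission heavily.

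**The case against.** A chi-square test of a randomised binary secondary outcome is conventional and valid, and the trial is not powered on remission. That stands, and it limits the point to efficiency and consistency.

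The size of the gain is unknown. The 0.5 in the sample-size section is the correlation between baseline and follow-up levels of depression assumed for the ANCOVA of the self-reported primary outcome. It cannot be read as the correlation between IDS-SR and an interview diagnosis. That also stands, which is why a range is given.

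Duration is not wholly ignored. The primary and secondary analyses are to be repeated in the two duration subgroups, which a chi-square test can do, and the primary model omits duration too. This is fair: leaving out duration is not peculiar to remission. The reason to include it here is that it is a minimisation factor.

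Three stronger readings are tempting, and the document supports none of them:

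- **The planned moderator analyses cannot be carried out for remission.** "Moderating effects of level of treatment-resistance and childhood trauma will be investigated by including an interaction effect" follows directly after the chi-square sentence, and a chi-square test cannot hold such a term. But the only models named are the general linear models for continuous outcomes, and nothing says that moderation of remission is planned. This is an ambiguity, not a contradiction.
- **Chance imbalance in severity is left to distort the result.** In the intention-to-treat sample, minimisation already limits imbalance in severity bands and duration. What remains is mainly imbalance within bands.
- **Severity and two further factors are ignored.** Baseline severity is itself one of the two minimisation factors, so two are left out, not three.

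**Conclusion.** The point holds as a free improvement to a secondary analysis. The plan fixes an unadjusted test for remission while adjusting its primary outcome for baseline IDS-SR and minimising on severity and duration. The cost is about 1 to 2 power points at a latent correlation of 0.2, 2 to 4 at 0.3 and about 7 at 0.5, with some conservatism when the factors are strongly prognostic.

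These figures rest on 43 analysed per arm, assumed remission rates and assumed prognostic strength; the document supplies only the first. A reader might infer that the chi-square result would be biased or prone to false positives. The calculations show the opposite: size is at or slightly below 5%. The sample size is untouched.

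**What to change.** Replace the chi-square sentence with a logistic regression of remission at the first follow-up on condition, continuous baseline IDS-SR and episode duration. Report the odds ratio and the standardised (marginal) risk difference, each with a 95% confidence interval. The risk difference matters because the adjusted odds ratio is conditional on the covariates and does not compare directly with crude rates. Keep the crude rates as description. When the analysis is repeated within duration subgroups, the duration term drops out.

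State whether moderation is meant to cover remission. If so, fit condition*moderator in this model; if not, say that moderation applies to the continuous outcomes only.

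The cost is one or two sentences and no new data. One caution: at 20% vs 40% the model rests on about 43 × 0.20 + 43 × 0.40 ≈ 26 remissions, so it should stay this small, and any interaction for remission should be labelled exploratory.
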